#### 7.5.5.3 *Unscheduled postnatal visits*

Women will be encouraged to attend the clinic if they or their baby become unwell during the follow-up postnatal period. Physical examinations and relevant blood samples will be conducted to guide management. Any illness will be treated as appropriate and according to standard local care. The date of attendance, diagnosis and treatment will be recorded on the CRF, and any adverse events reported according to standard procedures. Clinical care will also be provided for women who attend because of their own illness, but this will not be recorded as part of the study.

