##### 4.1.1.2 Safety

Treatment with DP has been shown to be safe in the 2nd and 3rd trimester of pregnancy. A single course of DP is safe for use in the 2nd and 3rd trimesters, and is recommended by WHO for treatment of malaria in the 2nd and 3rd trimester and has been the first-line treatment for this indication in Papua, Indonesia, for over 10 years. The main safety concern is a dose-dependent QTc prolongation associated with piperaquine, similar to that observed with other antimalarials like chloroquine, but less severe than with halofantrine and quinine. Clinical data do not suggest any association with arrhythmias when used as a single three-day course for treatment. The experience, however, with monthly dosing is more limited; approximately 1,000 women have received either 3-course or monthly IPTp-DP in Kenya, Uganda, and an ongoing IPTp-DP trial in Indonesia (STOPMIP-Indonesia).

There has been no indication that IPTp-DP is associated with an increased risk of congenital malformation or pregnancy loss (the existing evidence in Africa suggest a 61% [95% CI 12-83] reduction in the risk of foetal loss compared to SP [fixed effect meta-analysis conducted for this application]). Because of its slow elimination, monthly doses of DP could result in dose accumulation of piperaquine. Nevertheless, there is no evidence to date that the risk of QTc

prolongation increases with each subsequent monthly course, likely because piperazine-associated QTc prolongation is transient and lasts for a few days only. The magnitude of transient QTc prolongation remained constant and was similar after  $\geq 12$  monthly courses compared to a single course in a study of Ugandan children provided with 18 monthly courses of DP from 6 to 24 months of age.

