#### 7.4.2.2 Safety

1. QTc-prolongation
2. Congenital malformations
3. Maternal mortality
4. Other SAEs and AEs

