#### 10.2.4 Reporting adverse event procedures

All SAEs will be reported to the in country principal investigator or an assigned representative within 24 hours of the staff becoming aware of it, using an SAE form, which should be completed and sent electronically. The SAE form asks for nature of event, date of onset, severity, corrective therapies given, outcome and causality (i.e. unrelated, unlikely, possible, probably, definitely). The responsible study clinician should assign the causality of the event.

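### Section 7.5.5.3 tells sites not to record the mother's own illness at unscheduled postnatal visits, against the protocol's adverse-event rules

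*Protocol*

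**What the plan says.** Section 7.5.5.3 opens by addressing mother and child together: "Women will be encouraged to attend the clinic if they or their baby become unwell during the follow-up postnatal period". After providing for examination and treatment, it sets a recording rule: "The date of attendance, diagnosis and treatment will be recorded on the CRF, and any adverse events reported according to standard procedures". Its last sentence then takes the mother out again, offering clinical care to "women who attend because of their own illness, but this will not be recorded as part of the study".

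Elsewhere, maternal safety collection stays open after delivery. The safety outcomes in section 7.4.2.2 include "Other SAEs and AEs", with no end date and no exclusion of postnatal events in the mother. Section 10.2.4 states "All SAEs will be reported to the in country principal investigator or an assigned representative within 24 hours" of staff becoming aware, with no postnatal exception. Table 1 marks the study CRF, the physical examination and the adverse-event row at both the 1-week and the 6-8 week visit.

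**The concern.** A protocol may choose to stop collecting non-serious maternal events at delivery, but it then has to say so and keep its other sections in line. Here one section forbids recording and several others require it. A site has no rule for deciding which prevails, and the analysis plan cannot recover data that sites were told not to write down.

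The primary objective (5.1) asks whether the DP regimens are safe as well as superior. Section 9.3.2.2 names the number of SAEs as a count outcome to be compared by incidence rate ratio, and 9.3.3 examines safety by number of DP courses. All of this depends on events being ascertained in the same way at every site throughout follow-up. SP against DP is not masked, since the only placebo is for azithromycin (8.2.1), so conflicting recording instructions are better removed than left to local interpretation.

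**Working it through.** The protocol gives no figure to reproduce on this point. The check is a comparison of its own instructions.

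**Instructions that conflict with the non-recording clause**

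- *Section 7.5.5.3, preceding sentence.* The paragraph begins with illness in mother or baby, so its recording rule naturally covers both. If that rule is read as meaning babies only, the conflict inside the paragraph disappears, but every conflict below remains.
- *Table 1, adverse-event row.* Collection is marked at delivery, 1 week and 6-8 weeks, so it does not end at birth.
- *Table 1, footnote f.* Adverse events beyond the first 30 minutes after dosing are picked up by passive surveillance, with women encouraged to come to the clinic at any time between one study visit and the next. The clause in 7.5.5.3 closes that route for the mother's own illness after delivery.
- *Section 10.2.2.* Even mild adverse events are noted on the CRF.
- *Section 10.2.3.* The investigator must assess causality for each adverse event, which presupposes that the event is documented.
- *Section 10.2.4.* Every SAE is reportable, and 10.2.1.3 counts hospitalisation as serious.
- *Section 7.4.2.2.* The AE and SAE outcome has no postnatal cut-off.

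The narratives of the scheduled postnatal visits do not resolve the matter. Sections 7.5.5.1 and 7.5.5.2 name only the baby's treatment and clinical findings for the CRF, although Table 1 schedules maternal collection at those same visits.

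**What a literal reading of the clause puts at risk**

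1. Maternal death: still captured. Section 9.1.2 records vital status at scheduled and unscheduled visits and defines maternal mortality to 42 days.
2. Non-fatal maternal SAE: still reportable under 10.2.4. The weakness is that a general rule requires a report while the rule specific to this visit says nothing is recorded, so no clinic record need exist from which an SAE form would arise.
3. Non-serious event still present, or remembered, at the next scheduled visit: can be picked up through the Table 1 row. The interval between the two postnatal visits is about 6 - 1 = 5 to 8 - 1 = 7 weeks, so this relies partly on recall.
4. Common illness without hospitalisation and not thought related: exempt from reporting under 10.2.4.2. That section limits reporting; it does not say the event should go unrecorded.
5. Any other non-serious maternal event presented at an unscheduled postnatal visit and not elicited at the next scheduled one: unrecorded.

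The direct loss is item 5, with item 2 exposed to inconsistent handling.

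**Length of the window, as an illustration only**

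Inputs: enrolment at 16-28 weeks (7.2.1), postpartum follow-up of 6-8 weeks (6.1), and delivery at 40 weeks, which is an assumption because the protocol gives no figure. Antenatal follow-up is then 40 - 28 = 12 to 40 - 16 = 24 weeks. The postnatal share of maternal follow-up time runs from 6/(24 + 6) = 20% to 8/(12 + 8) = 40%. At the average booking of about 22 weeks (6.2.3), antenatal follow-up is 18 weeks and the share is 6/24 = 25% to 8/26 = 31%. These are shares of calendar time. They are not shares of events.

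**The case against.** The strongest reply is that other provisions contain the damage: SAEs under 10.2.4, deaths under 9.1.2, two scheduled adverse-event assessments in Table 1, and the exemption of common unrelated illness in 10.2.4.2. That reply stands as a limit on the size of the problem. It does not remove the contradiction, because it works only if sites disregard an express sentence written for this visit.

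A reader might also draw four stronger conclusions, none of which the documents support.

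- *That all maternal AEs and SAEs of the last 6-8 weeks are lost.* The provisions just listed rule this out.
- *That 20-40% of maternal safety information is missing.* That range is calendar time under an assumed 40-week delivery. It ignores the two scheduled assessments, and only women who attend unscheduled for their own illness are affected.
- *That late drug reactions or puerperal infections differing by arm would be missed.* Section 4.1.1.2 does say "Because of its slow elimination, monthly doses of DP could result in dose accumulation of piperaquine", but that concerns accumulation, and the same section describes the associated QTc prolongation as transient, lasting a few days. Azithromycin is a single two-day course at enrolment, which is 12-24 weeks before delivery on the 40-week assumption, and the product information gives a half-life of 35-40 hours. Nothing in the protocol points to a puerperal effect.
- *That the clause biases the comparison between arms.* It applies to all arms alike. The open SP-versus-DP comparison leaves room for recording to differ, but the protocol gives no ground for saying that it would.

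It can also be said that stating an end date for non-serious maternal events would reconcile the text just as well. That would be coherent, but it would narrow an outcome that Table 1 and 7.4.2.2 currently leave open to the end of follow-up.

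**Conclusion.** The point holds as an internal contradiction with a limited but real effect on safety ascertainment. If sites follow section 7.5.5.3 literally, non-serious maternal adverse events presenting between postnatal visits may go unrecorded in all arms, and consistent recognition of non-fatal maternal SAEs is put at risk even though their reporting remains mandatory. The expected effect is under-ascertainment, not a built-in imbalance.

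The number or proportion of events affected cannot be computed: the protocol gives neither maternal adverse-event rates nor the expected frequency of unscheduled postnatal visits. The conclusion rests on the wording alone and on the assumption that at least some sites would apply the clause as written.

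**What to change.** Delete the non-recording clause from section 7.5.5.3. In its place, state that unscheduled postnatal visits for the mother's own illness, up to the 6-8 week visit, are recorded on the same sick-visit and AE/SAE forms used in pregnancy under section 7.5.3, and that these events enter the maternal safety comparison. Add the mother to the CRF recording sentences in 7.5.5.1 and 7.5.5.2 so that they agree with Table 1.

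The cost is a short protocol edit and slightly more data entry. Sites already see and treat these women, and the forms exist. The edit should be made before enrolment, which the registration table in 2.3.1 shows as not yet started, because events that were never written down cannot be reliably recovered later.

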## 7.6 SAMPLE SIZE

### 7.6.1 Primary endpoint

#### 7.6.1.1 *Rationale behind sample size calculations*

The study is designed based on three main goals:

- a) to provide 80% power as a standalone trial to detect  $\geq 20\%$  relative reduction ( $RR=0.80$ ) by IPTp-DP in the primary endpoint from 21.3% in the SP arm, and
- b) to provide at least 80% power to detect a further relative reduction of 25% by IPTp-DP+AZ relative to IPTp-DP alone, and
- c) to take the existing evidence into account of the effect of IPTp-DP alone, such that on completion, a prospective meta-analysis combining the new evidence with the existing evidence on the effect of IPTp-DP versus IPTp-SP would have  $\geq 80\%$  power to detect a 17% relative reduction ( $RR=0.83$ ) in the same primary composite endpoint. The 17% (95% CI -10 to 37) reduction is based on the pooled effect size obtained from a fixed-effects meta-analysis of the previous two trials from Kenya and Uganda conducted for this protocol.

#### 7.6.1.2 *Sample size for a standalone trial*

The sample size calculations for the standalone trial were conducted using PASS software. The total sample size will be 4,680 women (1,560 per arm) across three countries pooled. A sample size of 4,020 women (1,340 per arm) will achieve 80% power trial to detect a  $\geq 20\%$  reduction in the primary endpoint from 21.3% with IPTp-SP to 17.0% ( $RR=0.80$ ) ( $\alpha=0.05$ ) (90% power to detect a 23.0% reduction). 4,035 (1,345 per arm) women are required to allow for 1 interim analysis using the Lan-DeMets spending function with O'Brien-Fleming type boundaries to preserve the overall two-sided type I error rate for efficacy (see.10.1.3, page 45).

We will recruit 4,680 women (1,560 per arm) to allow for 13.7% loss to follow-up, which is approximately double the rate of loss to follow-up for this same primary composite endpoint in our recently completed MiP trials in Malawi (N=1873, across 2 arms) and Kenya (N=1546, across 3 arms). These trials involved similar sample sizes per country as in the proposed study, however the higher rate of loss to follow-up is used for our current sample size calculations since not all hospitals will have been part of the previous studies.

This same sample size of 1,340 completers per arm also provides 80% power to detect a further 22.8% reduction ( $RR=0.772$ ) from 17.0% in the IPTp-DP alone arm to 13.1% in the IPTp-DP+AZ arm ( $\alpha=0.05$ ) (or 90% power to detect a 26.1% reduction [ $RR=0.739$ ] from 17.0% to 12.6%). The 21.3% primary endpoint prevalence in the control arm is the observed mean prevalence in the IPTp-SP arms of our previous trials in the same sites in Kenya and Malawi, which also provided LLINs on enrolment, and in observational cohort studies in Tanzania.

#### 7.6.1.3 *Power of updated prospective meta-analysis comparing IPTp-DP alone vs IPTp-SP*

The power calculations for the updated meta-analysis were conducted using the Metapow package in STATA, which uses simulations to calculate the appropriate, 'evidence-based', sample size using the available information from previous trials. In addition to the existing two trials, information from a third trial (PROMOTE-II) will become available in 2017/2018. This relatively small 2-arm trial ( $n=391$  per arm) will be conducted in eastern Uganda using an identical design as the proposed study ([name] et al). The effect size of this PROMOTE-II trial was also set to 17% for the sample size calculation. An updated meta-analysis that takes the evidence from the 2 completed trials, the planned PROMOTE-II trial, as well as this new proposed trial into account, this same sample size of 1,340 completers per arm provides 84.9% power (95% CI 84.7-85.1) to detect a relative reduction of 17% in the same primary endpoint by IPTp-DP alone relative to the IPTp-SP arm (100,000 simulations,  $\alpha=0.05$ ).

### 7.6.2 Power calculations for key secondary endpoints

#### 7.6.2.1 *Foetal loss and neonatal mortality*

An overall sample size of 1,340/arm also provides 80% power to detect a 43.8% reduction in foetal loss/neonatal mortality from 4.6% in the SP arm to 2.6% with DP ( $RR=0.562$ ,  $\alpha=0.05$ ). The 4.6% estimate for this endpoint was the average observed in the SP arms in Kenya, Malawi and Tanzania. The 43.8% reduction is similar to the pooled effect size of 57% obtained from fixed effects meta-analysis from the trials in Kenya and Uganda.

#### 7.6.2.2 *SGA-LBW-PT*

This same sample size also provides 80% power to detect a 21.5% reduction in the composite outcome of SGA-LBW-PT, from 18.8% to 14.8% ( $RR=0.7852$ ,  $\alpha=0.05$ ), again allowing for 13.7% loss to follow-up. The 18.8% estimate is the observed average in Kenya, Malawi, and Tanzania, recalculated for this protocol using the new INTERGROWTH population reference's 10th percentile to define SGA.

#### 7.6.2.3 *Other secondary endpoints*

The sample size calculations for subgroups involved in the assessment of other secondary endpoints including immunological, nutritional endpoints are presented in Appendix VII. Description of other clinical , page 84.

### 7.6.3 Power calculations for cardiac monitoring and safety study

To detect a difference of 10 milliseconds (ms) in QTc prolongation observed between the first and last course of DP, a sample size of 68 women per arm are required (SD 25 ms [based on 1,002 observations in children], 90% power, two-sided  $\alpha=0.05$ , paired test). To account for 15% loss to follow-up, 80 women per DP arm will be recruited (160 in total).

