### 5.2 SECONDARY OBJECTIVES

1. To determine if monthly IPTp with DP plus a single course of AZ at enrolment, is superior to monthly IPTp with DP alone for reducing adverse pregnancy outcomes.
2. To determine the safety of monthly IPTp with DP by conducting nested cardiac monitoring study to specifically address whether previously documented transient QTc prolongation associated with DP increases in magnitude with subsequent courses as well as monitoring adverse drug reactions and adverse/severe adverse events.
3. To conduct, on completion of the trial, a prospective meta-analysis combining the evidence from this and previous trials to provide (with  $\geq 80\%$  power) definitive evidence on whether IPTp with DP is superior to the existing strategy of IPTp with SP for controlling malaria and reducing adverse pregnancy outcomes in areas with intense year-round malaria transmission and high SP resistance.
4. To determine if the level of SP drug resistance, assessed by molecular markers, affects the potential impact of IPTp-DP or IPTp with DP+AZ relative to IPTp-SP.
5. To determine the efficacy of IPTp with DP+AZ on curable sexually-transmitted and reproductive -tract infections (STIs/RTIs) relative to IPTp with SP and DP alone.
6. To determine the effect of SP and AZ on the intestinal and vaginal microbiomes of mothers, and the intestinal microbiomes of neonates relative to DP alone.
7. To determine the effect of AZ on the prevalence of macrolide resistance.
8. To build trial research capacity in Kenya, Malawi and Tanzania.

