## 7.3 INTERVENTIONS

### 7.3.1 Trial Medications and interventions

#### 7.3.1.1 Name and description of study arms

All women will be randomly allocated to receive one of three IPTp regimens at enrolment and at each subsequent monthly ANC visit during the 2nd and 3rd trimesters. The range will be 3 to 7 visits depending on the gestational age of the woman at enrolment and delivery. Because recruitment is restricted to 16-28 weeks gestation, a median of 4 to 5 courses is expected.

1. **IPTp-SP:** This is the control arm and consists of a standard single-day stat course of 3 tablets of quality-assured SP (tablets of 500 mg of sulphadoxine and 25 mg of pyrimethamine) provided at enrolment and at each subsequent monthly ANC visit in the 2nd and 3rd trimester.
2. **IPTp-DP:** 3 to 5 tablets of DP (tablets of 40 mg of dihydroartemisinin and 320 mg of piperaquine, based on bodyweight) daily for 3 days provided at enrolment and at each subsequent monthly ANC visit in the 2nd and 3rd trimester plus 1gr (as 2 x 500mg equivalent tablet of placebo AZ daily for 2 days at enrolment. The dose of DP is equivalent to the standard treatment (case-management) dose for malaria in adults recommended by WHO with a target dose (range) of 4 (2-10) mg/kg bodyweight per day dihydroartemisinin and 18 (16-27) mg/kg bodyweight per day piperaquine given once a day for 3 days for adults and children weighing  $\geq 25$  kg (36-60 kg: 3 tablets, 60-80 kg: 4 tablets,  $\geq 80$  kg 5 tablets). One 3-day course will be provided at enrolment and again at each subsequent monthly ANC visit in the 2nd and 3rd trimester. The weight at enrolment will be used to define the weight class to guide treatment both at enrolment and subsequent scheduled visits.
3. **IPTp-DPAZ:** 3 to 5 tablets of DP (based on bodyweight) daily for 3 days provided at enrolment and at each subsequent monthly ANC visit in the 2nd and 3rd trimester, plus 2 tablets of AZ (500 mg) daily for 2 days (2 g total over 2 days) at enrolment. The dose of AZ is the standard dose for the treatment of STIs/RTIs.

Table 2: Dosing regimen per course

| Study arm | Drug       | Number of tablets once daily per course |        |        |
|-----------|------------|-----------------------------------------|--------|--------|

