### **Pharmacokinetics:**

**500mg dose:** Cmax: 0.4mg/L; Half-life: 35-40 hours; Volume of distribution: 23-31 L/kg; Table 3

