### **Adverse Effects:**

Gastrointestinal: abdominal cramps, nausea, diarrhea, anorexia, pancreatitis  
Genitourinary: vulvovaginal candidiasis, renal failure  
Cardiovascular System: prolongation of QT interval  
Hepatic: hepatotoxicity, jaundice  
Hematologic: eosinophilia, thrombocytosis, lymphopenia  
Central Nervous System: headache, fatigue  
Endocrine/Metabolic: hyperglycemia  
Dermatologic: itching, nail discoloration

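### The first-versus-last-course QTc test is a clean test of DP accumulation only in the DP-alone arm; in the DP+AZ arm it estimates accumulation minus any azithromycin effect at course 1

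*Protocol*

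**What the plan says.** Secondary objective 2 (section 5.2) asks "whether previously documented transient QTc prolongation associated with DP increases in magnitude with subsequent courses". Section 7.6.3 turns this into a within-woman comparison: the sub-study is sized "To detect a difference of 10 milliseconds (ms) in QTc prolongation observed between the first and last course of DP", with an SD of 25 ms, "90% power, two-sided" alpha of 0.05 and a paired test. It requires 68 women per arm and recruits 80 per DP arm (160 in total) to allow for 15% loss. The same contrast and power therefore apply to both DP arms.

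Section 9.1.2.1.1 schedules one ECG before the first dose and one 4-6 hours after the third dose of every DP course.

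Section 7.3.1.1 gives the DP+AZ arm monthly DP "plus 2 tablets of AZ (500 mg) daily for 2 days (2 g total over 2 days) at enrolment". Table 2 places those AZ doses on days 0 and 1. The long summary (2.3.4) and Table 1 show DP only at all later courses.

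The AZ product information in section 16.9.2 gives "Half-life: 35-40 hours" and lists "Cardiovascular System: prolongation of QT interval" among the adverse effects. Section 11.7.1.2 cites a study of AZ given with piperaquine in pregnant women that found neither an interaction nor cardiotoxicity.

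**The concern.** A paired first-versus-last comparison isolates the effect of repeated DP only if nothing else that might move QTc differs between the two courses. In the DP-alone arm nothing in the regimen does, apart from the AZ placebo at enrolment. In the DP+AZ arm, AZ is present at the first course and absent at the last.

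Subtracting the pre-dose ECG within each course does not remove the difference. At course 1 the pre-dose ECG comes before any AZ, so the whole of any AZ effect stays in the course-1 change. Last minus first then estimates DP accumulation minus the AZ effect. Any positive AZ effect pulls that estimate down, which for a safety question is the falsely reassuring direction. Section 4.1.1.2 calls dose-dependent QTc prolongation with piperaquine the main safety concern, and 80 of the 160 women are in the affected arm.

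**Working it through.** **Inputs.** From 7.6.3: difference 10 ms, SD 25 ms (taken as the SD of the paired difference), two-sided alpha 0.05, power 90%, n = 68, loss 15%. From 7.3.1.1, Table 2 and 9.1.2.1.1: AZ on days 0 and 1, DP on days 0 to 2, ECG 4-6 h after the third DP dose. From 16.9.2: AZ half-life 35-40 h. Assumed: the extra QTc, *a* ms, that AZ adds to the course-1 post-dose ECG, because the documents give no value.

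**1. The protocol's own figure.** For a paired t-test the noncentrality is (10/25) × √68 = 3.298, which gives power 90.2%; with n = 67 it is 89.7%. So 68 is the smallest n that reaches 90%, and 68/(1 − 0.15) = 80. The arithmetic in 7.6.3 reproduces exactly. The issue is what the contrast estimates.

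**2. AZ exposure at the course-1 post-dose ECG.** With doses 24 h apart, the last AZ dose precedes the third DP dose by 24 h, so the ECG comes 24 + 4 = 28 h to 24 + 6 = 30 h after it. Assuming simple exponential decay, the fraction of that dose's level remaining is 0.5^(h/half-life):

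- lowest: 0.5^(30/35) = 0.55
- highest: 0.5^(28/40) = 0.62

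Residue from the day-0 dose adds to this. The exposure is residual rather than peak, but not negligible. By the next monthly course AZ has gone.

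**3. Effect on the DP+AZ arm.** The contrast estimates (true accumulation − *a*). With true accumulation of 10 ms, SD 25 ms and 68 completers:

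| Assumed *a* (ms) | Expected last minus first (ms) | Power to show an increase |
|---|---|---|
| 0 | 10 | 90% |
| 2 | 8 | 74% |
| 3 | 7 | 62% |
| 5 | 5 | 37% |
| 10 | 0 | 2.5% |

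The last row counts only significant increases. The two-sided rejection rate is 5%, but half of those rejections would be significant decreases.

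**4. No accumulation.** If DP does not accumulate at all and *a* = 5 ms, the same arm has a 37% chance of a significant false decrease.

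**5. DP-alone arm.** No active AZ is given, so *a* does not enter. Its 68 completers keep 90% power for 10 ms.

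**6. Pooling both arms.** With 136 completers the estimate is 10 − *a*/2. For *a* = 2 and 5 ms that is 9.0 and 7.5 ms, with power 99% and 93%. Power is high because n doubles, but the estimate is still biased by half the AZ effect.

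**7. Course 2 as the reference in the DP+AZ arm.** This avoids AZ but loses any rise from course 1 to course 2. If 10 ms built up evenly (an assumption), course 2 to last would capture 10 × 2/3 = 6.7 ms over four courses or 10 × 3/4 = 7.5 ms over five, the median range expected in 7.3.1.1. Power at n = 68 is then 58% or 68%.

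**The case against.** The strongest reply is that the objective is not lost. Section 7.6.3 sizes each arm separately, so the DP-alone arm carries a full-power test that AZ cannot touch. That stands, and it is why the point is not a fatal one.

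Second, the bias is conditional. The product information says only that AZ may prolong QTc. The co-administration study in 11.7.1.2 used 1 g a day for 3 days, more than the 2 g total here, and reported no evidence of cardiotoxicity. A reader might infer from the table that the sub-study is biased and that its 90% power fails. The documents do not support that: they give no AZ effect in ms, and it may be zero. Equally, 11.7.1.2 as reported gives no estimate or bound, so zero cannot be assumed.

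Third, 7.6.3 is a power calculation, and section 9.3.1 leaves analysis detail to a SAP that is not available here. Section 9.1.2.1.2 measures piperaquine and AZ levels just after the post-dose ECG, and 9.3.3 looks at safety by number of DP courses, alone and with AZ. These make adjustment possible. But neither section singles out the one course that contains AZ, and 7.6.3 itself fixes the contrast and claims the power for both arms.

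Two further inferences should be resisted. The amendment list shows AZ moving from monthly courses to one course, which might suggest that 7.6.3 was overlooked at that change; the superseded section is not available, so this cannot be shown. Nor does the point mean that individual women go unmonitored: ECGs are read at every course under 9.1.2.1.1, whatever contrast is tested.

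**Conclusion.** The concern holds in limited form, at moderate severity. In the DP+AZ arm the first-versus-last contrast is DP accumulation minus any AZ effect on the course-1 post-dose ECG, so it cannot be read as a test of accumulation alone. If there is an AZ effect, the error is towards reassurance: power to show a true 10 ms increase would be 74%, 62% or 37% for AZ effects of 2, 3 or 5 ms, against the stated 90%. The direction follows from the design. The size rests on assumed AZ effects, on doses 24 hours apart, on simple exponential decay for the residual exposure, and on 25 ms as the SD of the paired difference. The DP-alone arm answers secondary objective 2 without this bias and with the planned power.

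**What to change.** - In 7.6.3 and the SAP, name the DP-alone first-versus-last comparison as the primary test of accumulation, and state that the 90% power holds for that arm.
- State that first-versus-last in the DP+AZ arm is not a test of accumulation alone, and do not pool the two arms' contrasts without allowing for AZ.
- Model QTc change by course over both arms, with a term for AZ at course 1. The between-arm difference in course-1 QTc change estimates the AZ effect and should be reported as such.
- If a course-2-to-last comparison is given for the DP+AZ arm, label it supportive, and note that it misses any rise from course 1 to course 2 and so has lower power.

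The cost is analysis wording only. ECGs before and after every course, and the drug levels, are already planned, and no extra women are needed.
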